|                                                                                                                                                                                                                                                                 |                                                                                                                                                                                                                                                                                                                                                                                                                                                                 |                                                                |                       |
|-----------------------------------------------------------------------------------------------------------------------------------------------------------------------------------------------------------------------------------------------------------------|-----------------------------------------------------------------------------------------------------------------------------------------------------------------------------------------------------------------------------------------------------------------------------------------------------------------------------------------------------------------------------------------------------------------------------------------------------------------|----------------------------------------------------------------|-----------------------|
|                                                                                                                                                                                                                                                                 | a categorical scale with response options < 3 years of high school; 3 or more years of high school; some education beyond high school; completed tertiary or higher education                                                                                                                                                                                                                                                                                   | for each category will be reported.                            |                       |
| A range of additional measures will be collected for the purposes of answering questions about pain, and for subsequent analyses of potential mediating effect on clinical outcomes. These measures will not be used, however, to determine treatment efficacy. |                                                                                                                                                                                                                                                                                                                                                                                                                                                                 |                                                                |                       |
| *Quantitative Sensory Assessment: Pressure pain threshold                                                                                                                                                                                          | Pain pressure threshold (PPT) will be assessed using pressure algometer with probe size 1 cm  and rate of pressure increase of 30 Pa/s. The probe is pressed into the greater trochanter of the femur with gradual increase of pressure. The test stops once the sensation of pressure changes to pain (i.e. threshold). 3 reps with 30 sec interval and mean value will be calculated.                                                             | Higher value indicates less sensitivity to pain.               | Baseline and 3 months |
| *Quantitative Sensory Assessment: Wind up Ratio                                                                                                                                                                                                                 | The perceived intensity of a single pinprick stimulus (256 mN pinprick) will be compared to a series of 10 repetitive stimuli of the same intensity, applied at a rate of 1/sec with an area of 1 cm  . Participants will be asked to give pain rating for the single stimulus and a pain rating for the series of 10 stimuli. Repeated 5 times. Mean value will be calculated                                                                      | Higher values indicate greater sensitivity to pain.            | Baseline and 3 months |
| *Quantitative Sensory Assessment: Conditioned pain modulation (CPM)                                                                                                                                                                                | CPM will be assessed as the change in pain perceived in one body region as a result of pain induced in another body region. PPT will be measured over the test hip. Participants will immerse their contralateral foot of the measured side in cold water at ~12 degrees. When patient reports a pain intensity between 4-6 out of 10 the hand is removed from cold water and PPT will be measured again, the difference between pre and post measures the CPM. | Higher values indicate greater abnormality in pain modulation. | Baseline and 3 months |
| *Inflammatory cytokines                                                                                                                                                                                                                                         | Blood samples will be acquired and analysed for IL-6, TNF-alpha, CRP and other                                                                                                                                                                                                                                                                                                                                                                                  | Higher values indicate higher inflammation.                    | Baseline and 3 months |

|                                                                                                                                                                                                                                                                                                                                                                                                                                                                                                                                                                                                                                                                   |                                                                                                                   |                                                                                                                                 |                                 |
|-------------------------------------------------------------------------------------------------------------------------------------------------------------------------------------------------------------------------------------------------------------------------------------------------------------------------------------------------------------------------------------------------------------------------------------------------------------------------------------------------------------------------------------------------------------------------------------------------------------------------------------------------------------------|-------------------------------------------------------------------------------------------------------------------|---------------------------------------------------------------------------------------------------------------------------------|---------------------------------|
|                                                                                                                                                                                                                                                                                                                                                                                                                                                                                                                                                                                                                                                                   | inflammatory markers to be determined. Participants will be asked to fast 12 hours before providing blood sample. |                                                                                                                                 |                                 |
| Spreading of pain                                                                                                                                                                                                                                                                                                                                                                                                                                                                                                                                                                                                                                | Participants will be asked to shade body sites with the pain and determine and answer 14 items about their pain.  | Number of pain sites will be used to quantify the spreading of pain and question will determine likelihood of neuropathic pain. | Baseline, 3 months and 9 months |
| 
Please note:
 
*These secondary outcomes will only be collected if face-to-face assessments are permitted and deemed safe by the University of Melbourne and the Victorian Government (COVID-19).
 
**These secondary outcomes will be collected in the CHESM Human Movement Laboratory at the University of Melbourne if face-to-face assessments are permitted and deemed safe by the University of Melbourne and the Victorian Government (COVID-19). Alternatively, these secondary outcomes will be self-reported if face-to-face assessments are not permitted or deemed safe by the University of Melbourne and the Victorian Government.
 |                                                                                                                   |                                                                                                                                 |                                 |

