| Number of minutes during at least moderate intensity exercise | Participants will be instructed to wear a wearable physical activity monitor over the initial 3 months of the study period. Number of minutes during at least moderate intensity exercise will be based on heart rate data. With participant consent, de-identified daily heart rate data will be automatically uploaded to a cloud-based system (Fitabase – Small Step Lab) from the participant's wearable activity monitor account.                                                                                                                       | Higher indicates greater time being active                                                                                         | Throughout the initial 3 months |
| Co-intervention use                                           | Participants will complete a custom-developed table to                                                                                                                                                                                                                                                                                                                                                                                                                                                                                                       | Participants who indicate they have used a                                                                                         | Baseline, 3 months and 9 months |

|                                                                                                       |                                                                                                                                                                                                                            |                                                                                                                                                                                                                                  |                                 |

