|-------------------------------------------------------------------------------------------------------|----------------------------------------------------------------------------------------------------------------------------------------------------------------------------------------------------------------------------|----------------------------------------------------------------------------------------------------------------------------------------------------------------------------------------------------------------------------------|---------------------------------|
|                                                                                                       | indicate the frequency of use (over the past 6 months) of a range of pain and arthritis medications and co-interventions.                                                                                                  | drug/supplement at least once a week in the past month will be reported as a current user of the relevant medication. Participants who have used a co-intervention once in the past 6 months will be reported as a current user. |                                 |
| Adverse events                                                                                        | Recorded by participants using a custom-developed table.                                                                                                                                                                   | Proportions of participants experiencing adverse events will be reported.                                                                                                                                                        | 3 months and 9 months           |
| Expectation of treatment outcome                                                                      | Rated using a Likert scale with anchors of “no effect at all” to “complete recovery”                                                                                                                                       | The number and proportion of participants selecting each response option will be reported.                                                                                                                                       | Baseline                        |

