### 5.4 Enrolment and Randomisation Procedures

Screening will be conducted via online screen then over the telephone as outlined above. Participants will be enrolled into the study once the informed consent process has been completed and they have completed the baseline questionnaire (on a web-based platform (REDCap) or via post) and baseline assessment at the University of Melbourne. If face-to-face appointments are not permitted by the University of Melbourne and the Victorian government (i.e. COVID-19), participants will be enrolled into the study once the baseline questionnaire has been completed. Each participant will receive a unique study ID and this will be documented in the participant’s record/database in addition to all study documents.

The randomisation schedule will be prepared by the biostatistician (permuted block sizes 6 to 12) stratified according to therapist (to control for therapist variation). The schedule will be stored on a password-protected website (REDCap) maintained by a researcher not involved in either participant recruitment or administration of primary/secondary outcome measures. Group allocation will be revealed by this same researcher after baseline primary/secondary outcomes have been completed.

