### **5.7 Trial Closure**

For each participant, the follow-up duration is 9 months from randomisation. At this point, final assessment will take place and no further data collection or monitoring will occur for that participant.

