## 8. INTERVENTION

This 9-month study includes 3-month exercise programs delivered by a physiotherapist followed by a continuation of the exercise program independently for a further 6 months. Participants in both groups will attend 9 online treatment sessions via Zoom, over the first 3 months. Once per week over the first 6 weeks and fortnightly thereafter. The first session will be up to one hour with subsequent sessions up to 30 minutes. Physiotherapists will provide participants with home-based strengthening exercises in paper format, containing exercise instructions. Participants in both groups will be prescribed exercise dosage (i.e. frequency, intensity, time) according to the American College of Sports Medicine (ACSM) recommendations. A 2017 meta-analysis in this area demonstrated that exercise programs prescribed in accordance with ACSM dosage recommendations resulted in greater symptom improvement compared to exercise programs with questionable concordance to ACSM dosage recommendations. Feasibility and acceptability of aerobic and strengthening exercise prescribed according to ACSM dosage recommendations has been demonstrated in our recent pilot study (HREC. 1851762). Participants will be provided with an ankle-cuff weight and resistance bands. Participants will also receive a wearable activity monitor to wear daily for the initial 3 months of the study.

**Strengthening only:** Participants will be instructed by the physiotherapist how to perform 5-6 lower limb strengthening exercises, including how to use equipment such as ankle cuff weights and exercise resistance bands. Initial sessions will involve 1 to 2 sets of 8 to 12 repetitions at an intensity deemed by the participant to be at least 'hard' ( $\leq 7$ ) on the modified Borg Scale of rating of perceived exertion (RPE). The dosage will increase as appropriate to 3 sets at 'hard to very hard' (between 7 to 8) on modified RPE Borg Scale (*Modified Borg Scale; 10 is maximal effort*). Strengthening exercises will take approximately 30 minutes per session. Participants will be asked to complete these three times per week at home.

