## **10. STATISTICAL METHODS**

### **10.1 Sample Size Estimation**

Primary endpoints of the trial are between-group differences in change in average overall hip pain intensity and change in physical function (Western Ontario and McMaster Universities Osteoarthritis Index) at 3 months. In OA trials, the minimum clinically important difference is a change in pain of 1.8 units (out of 10) and change physical function of 6 units (out of 68). Based on our recently completed RCT in hip OA, we assume a between-participant standard deviation of 2.2 for pain and 13 units for physical function and a baseline to follow-up correlation of 0.46 for pain and 0.40 for physical function. To achieve 90% power and 5% significance level we require 83 participants per group. Allowing for a 15% loss to follow-up rate (informed by previous hip OA trials), we aim to randomise a total of 196 participants over a period of 30 months.

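### At 3 months, the six-month rule for non-drug co-interventions counts use before randomisation as current use and tends to dilute any between-arm difference in use during treatment

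*Protocol*

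**What the plan says.** The co-intervention row of the outcome table in protocol section 4.6 lists the time points as "Baseline, 3 months and 9 months". It describes one participant-completed table, used to "indicate the frequency of use (over the past 6 months) of a range of pain and arthritis medications and co-interventions". No other recall period is given for any time point.

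Two classification rules follow. For medicines, a participant who has used a "drug/supplement at least once a week in the past month will be reported as a current user of the relevant medication". For co-interventions, which the row names separately from medicines, the rule is: "Participants who have used a co-intervention once in the past 6 months will be reported as a current user".

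The timing comes from elsewhere in the protocol:
- Section 5.7: "For each participant, the follow-up duration is 9 months from randomisation".
- Section 5.4: "Group allocation will be revealed by this same researcher after baseline primary/secondary outcomes have been completed".
- Section 8: "Participants in both groups will attend 9 online treatment sessions via Zoom, over the first 3 months".
- Section 10.1 places the primary endpoints at the same visit; for function, "change in physical function (Western Ontario and McMaster Universities Osteoarthritis Index) at 3 months".

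**The concern.** A six-month look-back answered 3 months after randomisation reaches back before randomisation. Someone who had, say, a single massage two months before enrolling, and none since, meets the rule for a current user at the end of the guided programme. The reported proportion is then not the proportion who used other care during treatment.

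Both primary outcomes are self-reported, and a reader will turn to this row to ask whether other care helps to explain a difference, or a lack of one, at 3 months. Use before randomisation is equal between arms in expectation. Mixing it in therefore tends to make the arms look more alike than they were during treatment, so the error leans towards false reassurance.

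**Working it through.** **The plan's own figure.** The protocol gives no co-intervention rates to reproduce. Its one relevant calculation is the sample size in section 10.1. For function, n per group = 2 × (1.960 + 1.282)² × 13² × (1 − 0.40²) / 6² = 2 × 10.51 × 141.96 / 36 = 82.9, so 83; then 83 / 0.85 = 97.6, so 98 per arm and 196 in total. This matches the protocol (5% taken as two-sided). Co-intervention use does not enter it.

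**Windows.** Inputs: assessments at 0, 3 and 9 months; time zero at randomisation (section 5.7); look-back of 6 months for non-drug co-interventions and 1 month for drugs and supplements (section 4.6). The window at time t is t − 6 to t, or t − 1 to t, in months from randomisation.

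| Assessment | Non-drug window | Months before randomisation | Drug/supplement window |
|---|---|---|---|
| Baseline | −6 to 0 | 6 of 6 | −1 to 0 |
| 3 months | −3 to +3 | 3 of 6 | +2 to +3 |
| 9 months | +3 to +9 | 0 of 6 | +8 to +9 |

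Only the non-drug rule at 3 months straddles randomisation. These windows are approximate, since baseline is completed shortly before allocation.

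**Effect on the between-arm difference.** Let p be the share who used a co-intervention in the 3 months before randomisation (equal in both arms in expectation) and u the share who used it during treatment. Every prior user counts as a current user whatever happens later. So:
- true difference = p × d₁ + (1 − p) × d₀
- reported difference = (1 − p) × d₀

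Here d₁ and d₀ are the between-arm differences in use during treatment among prior users and prior non-users.

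*If prior and later use are independent* (assumption), d₁ = d₀ and the reported share is 1 − (1 − p)(1 − u). With assumed use during treatment of 35% and 20%:
- p = 0.2: 48% and 36%, a difference of 12 points
- p = 0.4: 61% and 52%, a difference of 9 points
- p = 0.6: 74% and 68%, a difference of 6 points

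*If they are dependent*, the answer moves. Take p = 0.2 and the same true 15 points. If all prior users continue in both arms, d₁ = 0 and the reported difference stays at 15. If the whole difference comes from prior users stopping more in one arm, d₀ = 0 and the reported difference is 0. If d₁ and d₀ had opposite signs, the reported difference could even exceed the true one.

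**What the data still show.** The baseline table covers −6 to 0. A baseline non-user who reports use at 3 months must have used it after baseline, apart from recall error and any gap between baseline and randomisation. A participant who reports no use at 3 months had none during treatment. The ambiguity is confined to baseline users who also report use at 3 months: continued use cannot be told from use that stopped before randomisation.

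**The case against.** The case against giving this weight has four parts.

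**The measure is minor.** It is a descriptive secondary outcome and enters no analysis stated in the synopsis or section 10.3. Use of other care after randomisation does not bias an intention-to-treat comparison in a comparative-effectiveness trial; it only helps to interpret it. This stands, and it limits the consequence. It does not make the reported proportion right.

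**Eligibility already removes some prior use.** Section 5.2.2 excludes hip injections in the past 3 months and hip surgery in the past 6 months. For those, p is close to zero and dilution close to nil. This stands, but most other non-drug co-interventions have no such exclusion.

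**The dilution figure is fragile.** Independence is doubtful, since people who used other care before enrolling may well be likelier to use it afterwards, and the rates are assumed. This stands: the factor 1 − p is an illustration, not an estimate.

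**The form is not shown.** The questionnaire is an attachment listed in section 15, and its 3-month wording may differ. If so, section 4.6 misdescribes it and still needs correcting.

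Three stronger readings are tempting and are not supported:
- That the item cannot show any difference between the arms during treatment. The difference tends to be diluted, not necessarily erased, and new use among baseline non-users remains comparable.
- That analgesic use is caught by the overlap. The past-month rule puts it wholly after randomisation at 3 months.
- That the medication table contradicts its own rule because it asks about six months while the rule needs the past month. The row is a short summary of an unseen form, which may record past-month frequency; this calls for a check, not a finding.

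**Conclusion.** The point holds for non-drug co-interventions at 3 months only. As the rule is written, about half of the window at the primary time point lies before randomisation. Prior-only users are reported as current users, and a between-arm difference in use during treatment will tend to be diluted. The size cannot be fixed from the protocol. Under independence it is the factor 1 − p; under the two dependent patterns shown, an assumed 15 points at p = 0.2 is reported as anything from 0 to 15.

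The conclusion rests on reading the single six-month recall as applying at every listed time point, which is what section 4.6 states. Drug and supplement classification, the 9-month window, the primary analysis and the sample size are unaffected. The rule is worth correcting because the correction is cheap and the row informs how the 3-month result is read.

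**What to change.** In section 4.6, and in the 3-month questionnaire if it carries the same wording:
- Set the recall and the user definition for non-drug co-interventions at 3 months to the time since baseline (past 3 months).
- Keep six months at the 9-month questionnaire, where it matches the interval since the previous assessment.
- Check that the medication table records past-month frequency, so that it supports the past-month rule; amend it if it does not.

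For 3-month questionnaires already returned with six-month wording, do not present the answers as use during treatment. Report new use by arm among baseline non-users, and say that continued use among baseline users cannot be separated from use that had stopped.

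The cost is a questionnaire wording change and a minor amendment. The baseline and 3-month windows will then differ in length. If the change is made while the trial is running, the 3-month data may be split between two definitions. In that case, the baseline non-user tabulation gives a measure of new use that can be formed under both wordings, and the reporting restriction alone may be the better choice if most questionnaires are already in.
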